### Sample size (Phases 1 and 2)

The sample will consist of magistrates and public servants from the judiciary who score a minimum of 7 points on the recruitment instrument (SRQ-20), which is available for online completion throughout the regional jurisdiction via an electronic platform integrated into TRT5’s intranet.

The sample size for Phase 1 of the study was determined with Soler et al. [23] as a reference, considering a minimum of 30 participants. For Phase 2, the study primarily referred to a meta-analysis conducted by Khoury et al. [39], which assessed the effectiveness of 8-week mindfulness-based interventions in healthy individuals and found an average dropout rate of 10 %.

To establish statistical significance, a sample size of 72 individuals was estimated using G*Power 3.1.9.2, based on a one-tailed *t*-test for independent samples with α=0.05, β=0.20, and Cohen's *d* = 0.6. Considering an approximate dropout rate of 25 %, which is higher than that found in similar studies, an estimated recruitment of approximately 90 eligible individuals for the intervention and control groups is anticipated.

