## Description of protocol

### Study design

This study consists of two phases. The first is a pilot study to develop the M-TBCT protocol, assessing its suitability and practicality within the judicial context. The second phase is an efficacy trial using a single-blind design with two groups: an M-TBCT intervention group and a waitlist control group. Inspired by Soler et al. [23], the first phase will involve a sample of 30 participants, divided into three blocks of 10, each receiving M-TBCT in eight weekly one-hour sessions. Participant feedback via a self-report questionnaire will guide protocol refinement.

The second phase, an efficacy trial, will have 90 participants randomly assigned to either the intervention or waitlist group, each receiving the same M-TBCT regimen. The M-TBCT protocol will be administered individually on a weekly basis, with each session lasting 1 h and totaling 8 online sessions.

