Randomization success will be determined by no significant differences between the groups regarding demographic and clinical characteristics. Continuous variables will be analyzed using Student's *t*-test, and categorical variables will be analyzed using chi-square or Fisher's exact tests. Longitudinal data (T0, T1, and T2) for both intervention and passive control (waitlist) groups will be tracked using the repeated measures Student's *t*-test. Spearman's correlation test will assess variable correlations. M-TBCT program efficacy will be evaluated using repeated measures ANOVA to examine the main effects of time and treatment and their interaction. McNemar's test will assess changes in mental disorder risk classification after M-TBCT intervention. Effect sizes (Cohen's d) and 95 % CI will be calculated for intra- and inter-group comparisons (intervention and waitlist). The Bonferroni correction will be applied to adjust for various statistical tests.

The data will be analyzed through intention-to-treat (ITT), including all randomized participants in their initially assigned group, regardless of completing the treatment protocol. Per-protocol analysis will exclude participants with fewer than four sessions (50 % of the M-TBCT program). Attrition analysis (As-treated) will compare those who completed the protocol with those who responded only to the initial questionnaire. This study employs mixed-effects linear models (MLMs) for statistical analysis. Fixed variables, including depression, anxiety, and self-care, will be incorporated, whereas random variables will be introduced to capture intra-individual variation over time. This will enable modeling of unexplained individual differences not accounted for by the fixed variables, providing a robust approach to understanding the relationships between these variables and well-being throughout the study.

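### The stated 80% power for Phase 2 rests on a one-tailed test that the analysis section does not plan, and the 25% dropout allowance is added in a way that covers only 20% loss

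*Protocol article*

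**What the plan says.** All places are in the protocol article.

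- **Sample size (Phases 1 and 2).** The starting figure is "a sample size of 72 individuals was estimated using G*Power 3.1.9.2", and the calculation is "based on a one-tailed *t*-test for independent samples" with "α=0.05, β=0.20" and a standardised effect of 0.6. Dropout is put at roughly 25%, against the 10% average cited from a meta-analysis, and "an estimated recruitment of approximately 90 eligible individuals for the intervention and control groups is anticipated".
- **Study design.** The 90 appears without qualification: "The second phase, an efficacy trial, will have 90 participants randomly assigned". The abstract and the Participants section give the same number.
- **Statistical methods (Phases 1 and 2).** "M-TBCT program efficacy will be evaluated using repeated measures ANOVA", with main effects of time and treatment and their interaction. Effect sizes carry 95% confidence intervals, a Bonferroni correction is mentioned, and the level is 5% for every study hypothesis. The tails of the tests are not stated anywhere in this section.
- **Hypotheses.** H2 is worded in the direction of benefit.

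**The concern.** Two things in the sizing paragraph do not fit together.

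First, an allowance for loss is made by dividing the evaluable number by the proportion retained. Multiplying by one plus the loss rate gives too few people, and 90 is exactly what the multiplication gives.

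Second, the test used for sizing is not the kind of test planned for analysis. A one-tailed test at 5% spends its whole error rate on one side. A repeated measures F-test has no direction, and a 95% interval corresponds to a two-sided 5% test. If the analysis is two-sided, the 72 is too small for the stated beta before any dropout occurs.

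What is at stake is the power statement for the primary outcome, WHO-5. Beta = 0.20 tells the reader how much weight a non-significant result can bear, so it should hold for a test that the protocol actually plans.

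**Working it through.** **Inputs.** From the sample size section: d = 0.6, alpha = 0.05, power 0.80, one-tailed, 72 evaluable, 25% dropout, 90 recruited, and 10% dropout in the cited meta-analysis. The 1:1 allocation is from the randomization and blinding section.

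**Formula.** For a two-sample t-test with n1 and n2 evaluable, df = n1 + n2 − 2 and the non-centrality is d × √(n1·n2/(n1 + n2)). Power is the probability that a non-central t with these values passes the critical value (the 95th percentile of t if one-tailed, the 97.5th if two-sided).

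**Step 1: reproduce the 72.** With 36 per arm the non-centrality is 0.6 × √18 = 2.546 and df = 70. One-tailed power is 81.0%. With 35 per arm it is just under 80%, so 36 per arm, or 72 in total, is right for a one-tailed test.

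**Step 2: the dropout allowance.**
- As done: 72 × 1.25 = 90.
- What 90 retains at 25% loss: 90 × 0.75 = 67.5, so 67 or 68.
- What 90 retains at 20% loss: 90 × 0.80 = 72.
- What 72 evaluable needs at 25% loss: 72/0.75 = 96.

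**Step 3: power at d = 0.6, unadjusted t-test.**

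| Evaluable | How it arises | One-tailed | Two-sided |
|---|---|---|---|
| 67 (34/33) | 25% of 90 lost | 78.4% | 67.7% |
| 68 (34/34) | 25% of 90 lost | 78.9% | 68.4% |
| 72 (36/36) | 20% of 90 lost | 81.0% | 70.9% |
| 81 (41/40) | 10% of 90 lost | 84.9% | 76.0% |
| 90 (45/45) | no loss | 88.1% | 80.4% |

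Two-sided 80% power needs 45 per arm, or 90 evaluable, which at 25% loss means 90/0.75 = 120 randomised. With 67 or 68 evaluable, the effect detectable with two-sided 80% power is about d = 0.69.

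**Step 4: which error matters.** Down the one-tailed column, the dropout slip moves power from 81.0% to 78–79%, about 1 to 2 points below the 80% target. Across the row for 72, the change of sidedness costs 81.0 − 70.9 = 10.1 points. Together they take 81.0% to 67.7%, about 13 points.

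**Step 5: analyses that use the baseline.** The documents give no correlation r between baseline and post-intervention WHO-5, so r is an assumption here. Figures are two-sided, with 67 evaluable, d = 0.6 and equal variances.
- The time-by-treatment interaction on T0 and T1 alone is a comparison of change scores, with effective d = 0.6/√(2(1 − r)). Power is about 60%, 68%, 77% and 88% for r = 0.4, 0.5, 0.6 and 0.7.
- For a T1 comparison adjusted for baseline WHO-5, effective d = 0.6/√(1 − r²). Power is about 75%, 80% and 86% for r = 0.4, 0.5 and 0.6.

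**The case against.** Four points can be made for the plan.

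1. **The dropout slip is small, and the margin is deliberate.** This stands. On the one-tailed basis it costs 1 to 2 points, and 25% is well above the 10% cited. At 10% loss, 81 remain and one-tailed power is 84.9%. The slip alone would call for little more than a change of wording.

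2. **Dropout need not mean lost outcome data.** The protocol plans intention-to-treat with all randomised participants and also names mixed models. People who stop sessions may still complete the online questionnaires. With outcomes from all 90, two-sided power is 80.4%. This is possible, but the sample size section uses the 25% to raise the required number, which only makes sense if those participants do not contribute to the comparison.

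3. **One-tailed is openly declared and H2 is directional.** Also true, and the analysis section never uses the word two-sided. But a directional hypothesis does not make an F-test directional, and a 95% interval is conventionally two-sided. The mismatch between the two sections remains, as an inference from the planned methods.

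4. **The ANOVA may have more power than the t-test.** It may, or it may have less. A reader might infer from the 68% that the planned analysis will miss a true effect of 0.6 about 32% of the time. The documents do not support that. The 32% belongs to an unadjusted two-sided t-test, and the planned interaction matches it only when r is near 0.5. Nor do the documents show how a null result would be interpreted.

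**Conclusion.** The point holds in a limited form. Two errors in the sample size section are established. Ninety randomised does not retain 72 at the protocol's own 25% loss. And the beta of 0.20 is tied to a one-tailed test for which the analysis section has no counterpart. The first follows from the stated numbers alone. The second rests on reading the F-test, the 95% intervals and the undirected 5% level as two-sided.

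On the protocol's own unadjusted basis at d = 0.6, two-sided power is 70.9% with 72 evaluable and about 68% with 67 or 68, against a stated 80%. Most of the gap comes from sidedness. The power of the ANOVA that is actually named cannot be fixed from the documents, because it depends on a correlation they do not give. None of the figures here allow for the Bonferroni correction.

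**What to change.** Rewrite the power paragraph in the sample size section, keeping 90 randomised:

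- State that 90 leaves 72 evaluable at 20% loss and about 67 at 25%.
- Remove the one-tailed basis and state the test as two-sided at 5%.
- Give power of about 68% for d = 0.6 with 67 evaluable, labelled as the unadjusted t-test comparison, with a detectable d of about 0.69.

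If the authors want to claim more power through baseline adjustment, the statistical methods section must change too. It names no comparison of WHO-5 at T1 adjusted for baseline WHO-5, so a power claim resting on one would repeat the present mismatch. Name that comparison as the primary analysis, and report power over a range of assumed correlations (about 75%, 80% and 86% at 0.4, 0.5 and 0.6 with 67 evaluable), not only at the one value that happens to reach 80%.

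The cost is one rewritten paragraph and, if adjustment is credited, an amendment to the statistical methods. The unadjusted power becomes less favourable than the one now stated. No extra participants are needed.

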### Randomization and sequence generation (Phase 2)

The randomization process, via www.random.org (accessed on December 6, 2023), will be conducted using a computer-generated list of random numbers by the psychologist and lead researcher. After meeting the eligibility criteria and confirming interest in participating in the study, the participant will be invited by the psychologist-researcher to start the intervention (M-TBCT) or wait on the waiting list. Throughout the study, the participant will be informed by the psychologist about the asynchronous assessment deadlines (pre and post-intervention and at the 6-month follow-up).

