**Table utbl0001:** 

Subject area:	Psychology
More specific subject area:	Mindfulness and trial-based cognitive therapy
Name of your protocol:	Mindfulness-Integrated Trial-Based Cognitive Therapy
Reagents/tools:	N.A.
Experimental design:	This is a mixed methods study (quantitative-qualitative) divided into two phases: a pilot study to structure the M-TBCT protocol and test its acceptability and feasibility (phase 1) and efficacy trial of M-TBCT, single-blind, with two parallel arms (phase 2).
Trial registration:	Ensaiosclinicos.gov.br: U1111–1304–1781.
Ethics:	This study was approved by the Research Ethics Committee of the Federal University of São Paulo (CAAE 73,817,423.3.0000.5505). Participants will sign the Informed Consent Form online and data confidentiality will be guaranteed.
Value of the Protocol:	1) First randomized and controlled feasibility study that structures a protocol integrating psychotherapeutic tools validated in the literature and three assessment points (baseline, post-intervention and 6-month follow-up) 2) This randomized, controlled study aims to fill a gap in scientific evidence-based interventions to promote well-being in the judiciary 3) Improvements in well-being and self-care are expected, as well as a reduction in levels of anxiety, depression and cognitive distortions.

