### Participants

After the study protocol is publicized through institutional media such as videos, website, and emails, interested individuals will be selected using the SRQ-20. Those scoring 7 points or higher and meeting other eligibility criteria will be invited via email by the researcher as part of a care initiative aimed at learning and practicing evidence-based skills to develop autonomy and self-efficacy in promoting psychological well-being. During this invitation, participants will receive explanations about how the study will work, and those who agree to participate will sign the informed consent form. After completing the self-assessment questionnaires, the first thirty participants will proceed to phase 1 of the study. Upon completion of phase 1, other ninety participants scoring 7 or higher on the SRQ-20 and meeting other eligibility criteria will proceed to phase 2 of the study, being randomized into one of the two arms (M-TBCT or waitlist for treatment).

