### Therapist

Both studies anticipate the participation of the psychologist and researcher in this study. She is currently the only professional with completed training in both mindfulness strategies through the Mindfulness-Based Health Promotion (MBHP) protocol from the Open Mind Center at the Federal University of São Paulo and in Trial-Based Cognitive Therapy, as developed by [name] [13].

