### Implementation (Phase 2)

Based on the random list, after the participant has signed the informed consent form and been assessed for inclusion criteria and initial measures, they will be informed by the psychologist and lead researcher about starting the intervention or waiting on the waiting list. Those on the waiting list will be informed about their right to access the M-TBCT protocol at the end of the study if favorable results are obtained.

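### The Phase 2 randomisation list is made by the psychologist who also announces the arms and treats, so allocation concealment is not protected, and the single-blind label names no blinded party

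*Protocol article*

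**What the plan says.** The Protocol article gives three sections to randomisation and its implementation in Phase 2, and they state who does what.

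- **Making the list.** Randomisation "will be conducted using a computer-generated list of random numbers by the psychologist and lead researcher", with random.org as the source of the numbers (Randomization and sequence generation).
- **Acting on the list.** In the same section, "the participant will be invited by the psychologist-researcher to start the intervention (M-TBCT) or wait on the waiting list".
- **Telling participants their arm.** After consent, assessment of inclusion criteria and initial measures, "they will be informed by the psychologist and lead researcher about starting the intervention or waiting on the waiting list" (Implementation). Randomization and blinding gives the notifying role again.
- **Inviting candidates.** Those who reach the SRQ-20 cut-off and meet the other criteria "will be invited via email by the researcher as part of a care initiative" (Participants).
- **Treating.** "Both studies anticipate the participation of the psychologist and researcher in this study", and "She is currently the only professional with completed training in both mindfulness strategies" and in TBCT (Therapist).

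On blinding, the specifications table describes an "efficacy trial of M-TBCT, single-blind, with two parallel arms", and Study design says: "The second phase is an efficacy trial using a single-blind design with two groups". The section headed Randomization and blinding gives the 1:1 ratio, the source of the random numbers and who notifies participants. It does not say who is blinded.

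**The concern.** Concealment means that whoever decides on approaching and enrolling a candidate cannot know which arm that candidate would enter. Here the person who makes the list also stands at the point of entry and later gives the treatment. Someone in that position could, even without intending to, let a known assignment affect whom to invite next, when to do so, or how to settle a borderline answer on an exclusion item. No misconduct is alleged; the point is that the procedure should not rely on its absence.

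Selection of this kind can act on prognosis that nobody measures. The baseline comparisons planned under Statistical methods cover only recorded characteristics, so they would not reveal it. Adjusting for baseline WHO-5 would remove only the part that WHO-5 captures.

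The blinding label is a separate and lesser matter. The primary outcome is a self-rated well-being score, compared between people who know they had therapy and people who know they are waiting. A reader who sees single-blind may credit the trial with a protection that the text does not describe.

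**Working it through.** No arithmetic bears on this point. The check sets the sections side by side.

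**Allocation**

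1. *Who generates the list?* The psychologist and lead researcher (Randomization and sequence generation).
2. *Who announces the arm?* The same role (Implementation; Randomization and blinding).
3. *Who treats?* The psychologist-researcher, described as the only person currently trained in both components (Therapist).
4. *Who invites?* The researcher (Participants). The article does not say that this is the psychologist. It is probable, because the psychologist-researcher handles the other participant contacts that the article describes.
5. *Is the psychologist one person with the lead researcher?* The compound term psychologist-researcher and the singular pronoun in the Therapist section point to one person. If two people were meant, the psychologist would still be among those who make the list.
6. *Is anyone else given custody of the list?* No. Random.org appears only as the source of the numbers. No independent holder and no release step by a third party is described.
7. *Does the order of steps help?* Announcing the arm after consent, eligibility assessment and baseline means that the participant completes T0 without knowing the arm. It does nothing to keep the next assignment from the person who made the list.

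Steps 1, 2, 3 and 6 are stated or follow directly from the text; step 4 is likely. Together they describe an arrangement in which the enrolling side can hold the sequence.

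**Blinding**

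| Party | Blinded? | Basis |
|---|---|---|
| Participant | No | Told to start therapy or to wait (Implementation) |
| Therapist | No | Delivers the sessions (Therapist) |
| Outcome assessor | No | WHO-5 and the secondary scales are self-reported, completed online and asynchronously (Instruments), so the participant is the rater |
| Data analyst | Not stated | No section mentions it |

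The analyst is the only one of these parties who could still be blinded, and the article does not say so.

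**The case against.** The strongest objections are these.

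- **The article never says that allocation is unconcealed.** This is true. Non-concealment is an inference from the stated roles. It is more than silence that a fuller protocol could fill, because the article itself gives list generation and notification to the treating psychologist.
- **All ninety might be assembled first and randomised together,** in which case there is no next assignment to foresee. The Participants section can be read that way. The Implementation section, which speaks of each participant being informed after their own consent and baseline, leans towards individual release but does not settle it. On the batch reading the same person would still control both the roster and the list, so an independent holder would still be needed.
- **Eligibility leaves the recruiter little room.** The SRQ-20 cut-off of 7 is fixed, and candidates declare the exclusions themselves. This does narrow the recruiter's discretion. What remains is the order and timing of invitations, which the article does not fix, and items without a stated threshold, such as severe symptoms or regular practice of meditation.
- **The limitations already warn of self-report bias and of differing control-group experience,** and online asynchronous completion keeps an interviewer from influencing answers. Both points stand, and they reduce the harm done by the label. They do not make the label accurate.

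Two stronger readings are tempting and should not be adopted. A reader might infer from the date December 6, 2023 that the list already existed before recruitment. That date follows the web address as an access date, the randomisation itself is in the future tense, and the article does not date recruitment. A reader might also want to put a number on the bias. The article gives no figure for how many entries could be influenced or how far they would differ in prognosis, so any number would only restate its own assumptions.

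**Conclusion.** The point holds in this form: the article gives list generation, announcement of the arm and, in effect, treatment to one role, and probably invitation too, with no independent custody of the list. The arrangement as written therefore does not protect allocation concealment. It is not shown that assignments were or will be foreseen, nor that a list already exists. The size of any bias cannot be derived from the document.

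The conclusion assumes that the psychologist and the lead researcher are one person, or at least that the psychologist has the list. It is strongest if the psychologist also sends the invitations and if assignment is made participant by participant. Both are likely, and neither is stated outright.

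The single-blind label is unsupported, because no blinded party is named and the participant, therapist and rater all know the arm. That part is a wording correction. The allocation procedure is the part that has to be changed before Phase 2 randomisation, because no later analysis can reliably remove selection on unmeasured prognosis.

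**What to change.** 1. Have an existing lead researcher who neither recruits nor treats generate and hold the Phase 2 list. Study settings places lead researchers at TRT5 and at two universities, so a candidate should be available; the team must confirm that the person chosen has no recruiting or treating role.
2. That person releases each assignment to the psychologist only after consent, eligibility and the T0 measures are recorded. The article already puts the announcement after these steps; what is new is the independent holder and the recorded completion.
3. Amend the randomisation and implementation sections to state this, including who sends the invitations.
4. In the specifications table and Study design, replace single-blind with open-label with self-reported outcomes, or name the party actually blinded, for example an analyst working on masked arm codes.

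Permuted blocks and automated assessment reminders would be reasonable additions but are optional.

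The cost is a short amendment and a small coordination task for an existing team member. The target of 90 participants, the intervention and the outcomes stay as they are.

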### Randomization and blinding (Phase 2)

Participants meeting the eligibility criteria will be randomly allocated (1:1) to M-TBCT or the waiting list. Randomization is based on a random number service (http://www.random.org, accessed on December 6, 2023), and participants meeting eligibility criteria will be informed by the psychologist and lead researcher.

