### Statistical methods (Phases 1 and 2)

In Phase 1 of the study, a mixed methods approach will be employed, aligning with current recommendations for good clinical practice in feasibility analysis. These recommendations suggest that quantitative analyses should be primarily descriptive [[32], [40]]. In Phase 1, participant characteristics will be quantitatively described, while satisfaction with the program and feedback on it will be extracted from the self-report instrument and qualitatively grouped into major themes covered by the instrument. NVivo version 12 software will be used to organize and process the data.

Following the described results, an interpretative analysis and discussion of the findings will be conducted, drawing on the adopted literature. Qualitative information extracted from this instrument will also be used to explore the acceptability of the M-TBCT protocol among the target audience. An analysis predicting participant characteristics that increase or decrease adherence to M-TBCT will also be performed. According to Bowen [41], it is valid to emphasize that qualitative research methods are useful tools for understanding institutional culture.

In phase 2, categorical variables will be presented in numbers and percentages, and continuous variables will be expressed as mean values with standard deviation. Data normality will be assessed using Kolmogorov-Smirnov and Shapiro-Wilk tests. Variance homogeneity assumption will be tested with Levene's test. If the data does not meet the normality test, Bootstrapping procedures will be employed (1000 resamplings; 95 % BCa CI) to enhance result reliability, correcting for non-normal sample distribution and group size differences, and provide a 95 % confidence interval for mean differences [42].

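### Phase 2 allocation is described only as a 1:1 random-number list; baseline WHO-5, known before the arm is disclosed, is neither balanced nor listed as a covariate

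*Protocol article*

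**What the plan says.** The Study design section says that the efficacy trial "will have 90 participants randomly assigned to either the intervention or waitlist group". Allocation is then described in three subsections:

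- Randomization and sequence generation: the process "will be conducted using a computer-generated list of random numbers by the psychologist and lead researcher", with random.org as the source.
- Implementation: people are told to start or to wait, on the basis of the list, "after the participant has signed the informed consent form and been assessed for inclusion criteria and initial measures".
- Randomization and blinding: "Participants meeting the eligibility criteria will be randomly allocated (1:1) to M-TBCT or the waiting list", and "Randomization is based on a random number service".

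None of the three names blocks, strata or minimisation, and none says that there are none. Table 2 places the baseline WHO-5 in the same column as allocation.

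Under Statistical methods, efficacy rests on a repeated measures ANOVA with time, treatment and their interaction. Mixed models follow, whose named fixed variables include depression, anxiety and self-care. Randomisation counts as successful if no baseline characteristic differs significantly. Bootstrapping is described as "correcting for non-normal sample distribution and group size differences". The Therapist section names one therapist: "She is currently the only professional with completed training in both mindfulness strategies".

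**The concern.** The variable likely to predict follow-up WHO-5 best is baseline WHO-5. It is available before the arm is released, but the stated method does not use it to balance the arms, and the stated efficacy analyses do not list it as a covariate. In the ANOVA it enters as a time point. The treatment main effect therefore averages any baseline difference in, and the interaction is a comparison of changes, which is exposed to regression to the mean.

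At stake is precision in a trial of about 45 per arm, and how convincing the result looks if the arms differ visibly on the primary outcome at the start. The significance-test check on baseline would miss moderate imbalances.

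**Working it through.** **Inputs from the article:** 90 randomised 1:1; 72 evaluable; one-tailed α = 0.05; power 0.80; d = 0.6. **Assumed, not in the article:** T0–T1 correlation ρ of WHO-5, 0.5 with range 0.3 to 0.7; normally distributed WHO-5; the share of entrants below any cut.

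1. **The plan's own figure.** Noncentral t, one-tailed 0.05, d = 0.6: 35 per arm gives power 0.7996 and 36 per arm gives 0.809. So 72 is reproduced.

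2. **Arm sizes, if the list is unrestricted.** Binomial(90, 0.5): exactly 45:45 in 8.4% of lists; 40:50 or worse in 34%; central 95% range 36:54 to 54:36.
   - Power with all 90 evaluable: 0.881 at 45:45 and 0.877 at 40:50, a loss of 0.4 points.
   - Power with 72 evaluable: 0.809 balanced, 0.805 at the 40:50 ratio, 0.795 at the 36:54 ratio.

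3. **Baseline WHO-5 difference, no stratification.** SD = √(2/45) = 0.211 SD units. P(|difference| > 0.3) = 2[1 − Φ(0.3/0.211)] = 0.155. This uses 45 per arm, so it applies equally to one shuffled 45:45 list.

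4. **What a 0.3 SD difference does to an unadjusted comparison.** A T1 comparison moves by 0.3ρ: 0.09, 0.15 and 0.21 SD at ρ = 0.3, 0.5 and 0.7. A change comparison moves the other way by 0.3(1 − ρ): 0.21, 0.15 and 0.09 SD. At ρ = 0.5 either shift is 0.15/0.6, a quarter of the planned effect.

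5. **Whether the plan's check would notice.** With 45 per arm, a baseline t-test reaches p < 0.05 only above about 0.42 SD. A 0.3 SD difference has p of about 0.16 and would count as successful randomisation.

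6. **Gain from stratifying in two strata.** The split explains a fraction f = φ(z)²/[p(1 − p)] of the baseline variance, where p is the share below the cut and z its normal quantile. The remaining SD is 0.211√(1 − f).
   - Median cut: f = 2/π = 0.64, SD 0.127, P(|difference| > 0.3) = 1.8%.
   - 70%, 80% or 90% below the cut: about 3%, 4.6% or 8%.

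7. **Gain from adjusting.** In SD² units, a change score has variance 2(1 − ρ) and the baseline-adjusted outcome has 1 − ρ². The saving is (1 − ρ)/2: 35%, 25% and 15% at ρ = 0.3, 0.5 and 0.7. Adjusting only for the stratum at ρ = 0.5 saves 0.25f: 16% at a median cut (0.25 × 0.64) and about 9% at 90:10.

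**The case against.** The absence of blocks and strata is read from silence, in an article that condenses a fuller protocol. A reader might infer that arm sizes are left to chance, but a single shuffled 45:45 list also fits a 1:1 random-number list. The remark on group size differences does not settle it, because dropout also makes analysed groups unequal. This part of the objection stands. Either reading leaves baseline WHO-5 unbalanced, however, so the main point survives it.

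Simple randomisation is valid, and the standard error of an unadjusted comparison already allows for chance imbalance. A reader might infer bias; there is none in expectation. That also stands, and it limits the point to precision and credibility.

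Stratifying at 50, the screening cut-off given for WHO-5, might seem natural, with the drop to 2% as its benefit. The 2% needs a near-median cut. Entrants score 7 or more on the SRQ-20, so many may lie below 50, and the article gives no WHO-5 distribution.

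A reader might also infer that a plain list will overload the only therapist and delay starts after T0. That is a plausible secondary reason for blocking. But the article gives no Phase 2 intake schedule or capacity, and the three groups of 10 belong to the pilot, so no figure can be attached to it.

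Finally, blocks added to the present arrangement could do harm: the psychologist who makes the list also informs participants, so she would know the block sizes. This stands, and the fix has to meet it.

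**Conclusion.** The point holds as a worthwhile improvement on the method stated. Without stratification, a baseline WHO-5 difference above 0.3 SD arises in about 15% of trials, and the plan's baseline tests would usually not flag differences of 0.3 to 0.4 SD. The loss is of precision and credibility. Unequal arm sizes matter little: about 0.4 points of power at 40:50.

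Most of the recoverable precision comes from using baseline WHO-5 in the model: 25% less variance than a change comparison at ρ = 0.5, and 15% to 35% over ρ = 0.7 to 0.3. Stratification mainly protects visible balance. These gains rest on the assumed correlation and on normality. The phrase about bootstrapping is loose, since resampling does not even out arm sizes, but removing it would change no result.

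**What to change.** - In the randomisation subsections, state permuted blocks of randomly varying size (for example 4 and 6), stratified by baseline WHO-5 in two strata. If the full protocol already restricts the list, say so in the article.
- Fix the cut near the median expected in SRQ-20 positive entrants before the first allocation. If only the cut-off of 50 can be justified, stratifying there still helps, but less.
- Have the list generated and held by an existing team member other than the psychologist who enrols and treats. Release each arm only after consent and the baseline measures, and keep block sizes from her.
- Include baseline WHO-5 as a covariate in the efficacy model, preferably continuous, together with the stratum.

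The cost is protocol wording, a new list and a small task for one team member, with no extra participants. The downside is that blocks are slightly more predictable once arms are known; random block sizes and a list hidden from the enroller limit this.
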